## Abstract

**Background:**

Parkinson’s Disease (PD) affects movement and cognition, and physiotherapy, particularly treadmill gait training, has potential in addressing movement dysfunctions in PD. However, treadmill training falls short in addressing cognitive aspects and adherence. Virtual reality (VR) and gamification can enhance motor and cognitive retraining and improve adherence. People with Parkinson’s Disease (PWPD) have decreased motor skill learning efficiency, but tDCS can improve motor and cognitive learning.

**Methods:**

78 participants with PD will be randomly allocated in a 1:1:1 ratio to one of three groups: (1) treadmill + Gamified Virtual Reality Environment (GVRE) + tDCS training group; (2) treadmill + GVRE training group or (3) treadmill training group. Participants will follow a 6-week, 12-session treadmill gait training plan, gradually increasing session duration from 20 to 45 minutes. Participants in (1) and (2) will undergo a GVRE training protocol, with (1) also receiving tDCS for the first 20 minutes of each session. Assessments will occur at baseline, post-intervention, and at a 6-week follow-up. The primary outcome measure will be gait speed during single and dual-task performance. Secondary measures will include additional gait parameters, executive tests for cognitive performance, and clinical outcomes for disease stage, cognitive status, and physical condition.

**Discussion:**

This randomized clinical trial presents an innovative neurorehabilitation protocol that aims to improve gait and cognition in PWPD. The study also examines how tDCS can enhance motor and cognitive training. Results could contribute to enhancing the motor and cognitive state of PWPD through a GVRE and tDCS-based neurorehabilitation protocol.

**Trial registration:**

NCT05243394. 28/02/2024 –v3.2

## 1.- Introduction

Parkinson’s Disease (PD) is a neurodegenerative disorder mainly known to cause resting tremor, bradykinesia, postural instability, rigidity, and a highly variable, short-stepped gait [1–3]. People with Parkinson’s Disease (PWPD) also have a wide variety of non-motor difficulties that affect their daily activities. It has been recently shown that they present a slight cognitive decline at the early stages of the disease that aggravates with time [4]. This could explain why there is an increase in falls and freezing of gait while carrying out several tasks at the same time [5]. This combination of gait and motor or cognitive tasks is known as Dual Task (DT), and is related to gait impairments such as reduced speed and stride length, decreased symmetry and coordination and increased variability [6].

Since PD is a chronic disease that has no cure, pharmacological treatment with Levodopa is the mainstay for management of motor symptoms. However, as the disease progresses most patients need increasing doses and end up with side effects including dyskinesia and on-off fluctuations [7]. Levodopa improves hypokinetic gait in the early stages of the disease [8]. However, levodopa responsiveness on gait worsens with time, and some parameters, such as gait timing, are not affected by levodopa [8]. Moreover, the presence of non-motor symptoms such as cognitive impairment, depression or psychosis creates even more treatment challenges. In this context, physiotherapy has shown promising results as an effective tool in rehabilitating gait dysfunctions in PWPD through therapeutic exercise [9]. One of the most used therapies consists in walking on a treadmill several times a week, showing positive effects over physical performance in PD, improving walking economy and the specific gait kinematic parameters affected in PD: speed, stride length and gait variability [10–13]. The feasibility and safety of treadmill gait training at moderate and high intensities have both been well established in de novo PD [14].

However, this type of intervention fails to address the importance of cognition for safe walking [15]. PWPD also have difficulties in following exercise programs for extended periods of time due to fear of falling, lack of expectations, apathy, and fatigue [16]. Virtual Reality is a computer-generated technology that allows the user to interact with a virtual environment similarly to a physical place. In the Virtual Reality environment, PWPD have access to amplified feedback on their performance and are able to train both motor and cognitive abilities. This environment offers the chance to learn and retrain motor and cognitive strategies that may have been lost due to PD’s degenerative nature [17–19]. Current evidence presents Virtual Reality as a promising tool for PWPD that could optimize motor learning by offering a safe and realistic environment in which individualized and repeated motor function can be practiced while stimulating cognitive processes at the same time [19].

Gamification, which is generally defined as “the use of game design elements in non-game contexts” [20] seeks to recreate an environment to enhance experiences and motivation. Based on Ryan and Deci’s Self-Determination theory [21], participants would be driven by their need to grow and gain fulfillment, making gamification a more helpful tool in turning exercise into a more engaging activity, which could improve adherence [22, 23]. More specifically, gamification could be a beneficial tool for physiological, mental and cognitive functions, even though available literature on elderly populations is scarce so far [24].

A relevant factor in the rehabilitation of gait in PWPD is the efficiency with which motor skills are learned. In comparison with healthy individuals, PWPD show a reduced consolidation and automatization in motor skill learning, which they attempt to compensate for by recruiting additional brain regions and by altering the effective connectivity patterns [25]. Through practice patients are able to improve their performance, though their ability to learn new motor skills and consolidate the achieved skills remains affected [25]. In this sense, Transcranial Direct Current Stimulation (tDCS) is presented as one of the techniques of choice to improve the learning of motor skills in PWPD. However, this technique is currently a topic of intense scientific discussion due to the conflicting results from previous studies [25].

A systematic review by *Broeder et al*. [25] concluded that tDCS can have significant improvements on motor and cognitive functioning in patients with PD. Specifically, anodal-tDCS, which increases cortical excitability, showed positive effects on several parameters of gait performance in 5 out of 7 different studies, with one of them finding significant benefits of combining anodal-tdcs with physical training. tDCS has the capacity to enhance or suppress widespread neuronal activity, leading to the release of dopamine via motor networks within the basal ganglia-cortex-cerebellum system and other motor cortical regions [26]. According to research by *Frase et al*. [27], repeated anodal-tDCS sessions would be able to directly trigger plastic Long-Term-Potentiation-like effects in the human cortex.

Effects of tDCS on the improvement of motor functions may be caused by the activation of motor and prefrontal cortex regions, which may lead to the release of dopamine in PWPD, thus promoting the improvement of motor functions [28]. Current evidence also seems to point towards certain benefits of anodal-tDCS when combined with therapeutic exercise, such as an improvement of cognitive functions [29]. However, the diverse variations in stimulation parameters and target regions across different studies prevent definitive conclusions [28]. Within the realm of tDCS, various approaches have been suggested. Bi-hemispheric stimulation, while potentially cost-effective for concurrent cognitive tasks, lacks conclusive evidence at present [30, 31]. Even within this scarce body of evidence, no studies have provided insight on how its use in combination with a Gamified Virtual Reality Environment (GVRE) may influence motor and cognitive learning. Therefore, diving deeper in the short- and mid-term effects of gait training in a GVRE would help to delineate whether tDCS could provide any additional benefits in PWPD.

The aim of this three-arm RCT is to evaluate the effects of the inclusion of a GVRE to a 6-week treadmill training program with anodal-tDCS in PWPD on gait parameters during Single and Dual Task, clinical outcomes and executive functions; in comparison to a GVRE treadmill training program; and compared to a treadmill training as a control.

## 2.- Materials and methods

### 2.1.- Trial design

This is a prospective, single-blinded, single center, three-arm RCT. This study protocol follows the Standard Protocol Items: Recommendations for Interventional Trials (SPIRIT) guideline for clinical trial protocols.

The study will be conducted in Lleida, Spain, at the Lleida Institute for Biomedical Research [name]. Eligible participants will be randomly distributed in three groups: 1) treadmill gait training; 2) GVRE + treadmill gait training; 3) anodal-tDCS + GVRE+ treadmill gait training. Fig 1 shows a flow diagram based on the Consolidated Standards of Reporting Trials (CONSORT) for this study. Table 1 shows the planned schedule to address enrollment, assessments (at baseline, post-intervention and follow-up) and interventions.

**Fig 1 pone.0307304.g001:**
[figure not shown]
Flow diagram based on CONSORT.

**Table 1 pone.0307304.t001:** Schedule of enrollment, interventions and assessments.

	Study Period			
	Enrollment	Allocation	Post-allocation	Follow-up
Timepoint	-t_1_	t_0_	t_1_	t_2_
**Enrollment**				
Eligibility Screen	x			
Written Informed Consent	x			
Allocation		x		
**Interventions**				
Intervention G1			x	
Intervention G2			x	
Intervention G3			x	
**Assessments**				
Executive function assessment (Victoria Stroop test, Go/No-Go test)		x	x	x
Clinical outcomes (MoCA, UPDRS, H&Y, PDQ39, MiniBEST, FES-I)		x	x	x
Gait Assessment under Single and Dual Task conditions		x	x	x

Baseline assessments (T0) will provide information regarding motor, cognitive and clinical data before the intervention takes place. In the next session after the intervention is over, a post-intervention assessment (T1) will be carried out to know the effects of the training protocol as well as how both groups’ results compare. Finally, after 6 weeks post-training (T2), a follow-up assessment will be performed to measure how any results the participants may get through the intervention retain over time. All participants will perform their interventions at the same hour of the day and during the ON phase of medication to avoid any bias related to circadian rhythms or ON-OFF fluctuations. This measure will be encouraged by asking participants to take their medications 1 hour previous to meeting the researchers to be evaluated. All evaluations will follow the same timing restrictions. A researcher blinded to the participants’ allocation will conduct all assessments.

All procedures have been approved by the ethical committee of Hospital Universitari Arnau de Vilanova (CEIC-2231), and both the Helsinki Declaration and the Oviedo Convention will be followed [32, 33]. Spanish regulations regarding Biomedical Research will be met as well [34].

### 2.2.- Sample size

The sample size calculation was based on the study of Mirelman et al [35]. From this study, we assumed that gait speed during a treadmill dual-task assessment in PD patients would be approximately 1.01±0.23 m/s. From the study of *Hass et al*. [36] it was established that an increase of 0.22 m/s in gait speed would be considered clinically relevant. The GRANMO sample size calculator [37] was used to run an analysis of variance calculation.

With an alpha risk of 0.05 and a beta risk of 0.20, assuming a 10% withdrawal rate, and using a two-sided test, it will be necessary to include 26 subjects in each of the three groups.

### 2.3.- Participants

In total, 78 participants will be recruited mainly via the Hospital Universitari Arnau de Vilanova of the city of Lleida, as well as through contact with neurologists, local PD associations (Associació de Parkinson de les Terres de Lleida) and other methods such as distribution of fliers and contact with local news media.

The following inclusion criteria will be applied:

Aged 50 or olderIdiopathic PD (UKPDSBBC)Stage II–III in the Hoehn & Yahr (H&Y) scale during ON stateAbility to walk for 10 minutes independently without stop

The exclusion criteria will be the following:

Significant cognitive decline based on mini mental status examination (MMSE <23)Severe auditory or visual deficitsOther neurological/psychiatric conditionsAny kind of cardiovascular complications that contraindicates physical activityClinical history of any brain surgery or deep brain stimulation device

Subjects that must change their medication while participating in the RCT will be considered as non-retention subjects.

### 2.4.- Ethics approval

This study was authorized by the Comité d’Ètica d’Investigació amb Medicaments (CEIM)–Hospital Universitari Arnau de Vilanova, Lleida, Spain, with identifier CEIC-2231.

Any protocol amendments or changes will be notified to the ethics committee as well as updating all information in the clinical registry.

Participants will give their individual, signed written informed consent to participate in the study and will be thoroughly informed about all procedures that will be carried out by an evaluator. Adherence will be promoted with session reminders as well as progression tracking.

### 2.5.- Randomization and blinding

Randomization and allocation concealment will be performed using a random number generation computer technique. Randomization will be made by blocks with a size of 3 and stratified based on two covariables: age and disease stage. The ratio of assignment will be 1:1:1, and the randomized list will be generated through the Study Randomizer software by a blinded postdoctoral researcher who will not be involved in the study. Opaque, sealed envelopes will be used to conceal the allocation sequence, and opened only at the time of randomization in the presence of the study participants.

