Victoria Stroop Test, which will measure the ability to inhibit cognitive interference [49]. A total of 3 blocks with different words and color stimuli will be assessed, with time taken, responses made and interference as measuring units.Go/No-Go Test, which will measure the participant’s attention and response control [50]. A total of 80 stimuli will be provided, with 20% of those being fake signals that must be ignored. A total accuracy score based on participant responses will be calculated.

Clinical outcomes:

The following scales and tests will be used to assess clinical symptomatology as well as aspects related to quality of life and daily activity autonomy.

Unified Parkinson’s Disease Rating Scale–Part III (UPDRS): UPDRS will be used to assess and monitor PD related disability and impairments. Part 3 of this scale comprises an assessment of different aspects of motor function [51].

Hoehn & Yahr: The assessment using H&Y scale is based on issues of unilateral versus bilateral involvement and the presence or absence of postural reflex impairment [52].

Parkinson’s Disease Questionnaire 39 (PDQ39): This is a patient reported 39-item questionnaire and it assesses PD-specific health related quality of life and disease specific health status [53].

MiniBest Test: This 14-item test is used to assess dynamic balance based on anticipatory postural adjustments, reactive postural control, sensory orientation and dynamic gait [54].

Falls Efficacy Scale International (FES-I): FES-I is a 16-item self-administered questionnaire including a range of functional activities and is designed to assess fear of falling [55].

Montreal Cognitive Assessment (MoCA): MoCA is a 30-question test to assess cognitive function and it evaluates orientation, short-term memory, executive function/visuospatial ability, language abilities, abstraction, animal naming, and clock-drawing test [56].

Any information regarding all the above measurements can be found in http://www.scalesandmeasures.net/. Moreover, a semi structured interview will be added in regards to adherence to treatment, which will allow for a qualitative analysis to explore the experience regarding the GVRE.

Participants will be reminded not to inform the evaluator about their group assignment in order to ensure blinding.

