## 4.- Limitations

The main limitation on this study is the lack of a placebo anodal-tDCS group. This means that we will not be able to know whether any benefits that the tDCS group may achieve are related to the theoretical applications that tDCS has, or to the placebo effect. There is also no control over the inclusion of gamification elements, which are added to all interventions that use the GVRE. Another limitation is the lack of a treadmill training and anodal-tDCS group, which would allow us to know to which extent the GVRE adds to the treadmill and the tDCS treatments. However, previous studies have shown no benefits from tDCS combined with treadmill walking on kinematic parameters in PD [64]. For this reason, and also difficulties in achieving a larger sample size, the decision to not include a tDCS + treadmill group was taken. The current study group distribution will allow for clear views on the effects of a customized GVRE to a treadmill set-up, unconditioned by possible placebo effects from tDCS, as well as knowledge on tDCS effects when added to the intervention. Another limitation is also that there is no control on the subtype of PD that any of the participants may be suffering, or whether freezing of gait is present, which could bias the results obtained. Another limitation that should be noted is that currently there is no control over how much physical activity participants follow besides the training program. In some cases, participants feel more engaged to partake on more physical activity, and even though it will be asked to limit physical activity to the usual plus the training protocol, such indications could be ignored.

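### A single fixed block size of 3 for three arms lets anyone who tracks allocations within a stratum know the last one of each complete block, an avoidable risk to concealment

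*Protocol article*

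**What the plan says.** Section 2.5 of the protocol article fixes the scheme: "Randomization will be made by blocks with a size of 3 and stratified based on two covariables: age and disease stage". It adds: "The ratio of assignment will be 1:1:1". The list is produced by a researcher outside the study, and the allocation is hidden in opaque, sealed envelopes that are "opened only at the time of randomization in the presence of the study participants".

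On blinding, Section 2.1 says: "This is a prospective, single-blinded, single center, three-arm RCT". The text after Table 1 shows whose blinding is meant: "A researcher blinded to the participants’ allocation will conduct all assessments". Participants know their arm, since Section 2.7 says: "Participants will be reminded not to inform the evaluator about their group assignment in order to ensure blinding". Section 4 confirms that there is no sham stimulation: "The main limitation on this study is the lack of a placebo anodal-tDCS group". Section 2.6 has a physiotherapist supervise every session, and the arms differ by a screen with foot trackers and by scalp electrodes.

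The article gives no age cut-off, so the number of strata is not known. It does not say that block sizes vary or that the size is withheld from site staff.

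**The concern.** Three is the smallest block that 1:1:1 allocation to three arms permits, and so the most predictable. Envelopes and an outside list-maker hide the card and the list. They do not stop anyone from working out the next arm from the arms already given, and here those arms are visible to anyone near the sessions. Age and disease stage are known at screening, so a participant can be placed in a stratum before allocation once the age cut-off is known.

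What is at stake is selection bias. Someone who knows the next arm can bring an enrolment forward, delay it, or lean one way on an exclusion that needs judgement, such as sensory deficits or other neurological or psychiatric conditions (Section 2.3). A baseline difference created in this way would be mixed with the treatment effect on gait speed, and adjustment for measured covariates need not remove it.

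**Working it through.** **Inputs.** Block size 3, ratio 1:1:1, two stratifiers (Section 2.5); three arms, one centre (Section 2.1); 78 participants (Section 2.3). The number of strata is an assumption: 4 (2 × 2) or 6. The article states no predictability figure to reproduce.

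**Observer.** Someone who knows the block size and the earlier allocations in the stratum, and who always guesses the arm with most places left in the block.

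**Planned design, complete blocks.** The chance of a correct guess is 1/3 at the first place, 1/2 at the second and 1 at the third.
- Correct guesses: (1/3 + 1/2 + 1)/3 = 11/18 = 61.1%, against 33.3% by chance.
- Certain allocations: 1 in 3, so at most 78/3 = 26.

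**Incomplete last blocks.** The certain allocations number Σ⌊n_s/3⌋ over strata of size n_s. Each stratum can leave at most 2 participants over, and the total left over must be a multiple of 3 because 78 is.
- 4 strata: at most 6 left over, so at least (78 − 6)/3 = 24 certain.
- 6 strata: at most 12 left over, so at least (78 − 12)/3 = 22 certain.
- One stratum of 20, as an example: 6/20 = 30% certain, and (6 × 11/6 + 1/3 + 1/2)/20 = 59% guessed correctly.

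**Larger fixed blocks, size known.** With b places per arm, the expected number of certain allocations in a block is the expected length of its final run of one arm, 1 + (b − 1)/(2b + 1) = 3b/(2b + 1). The share is therefore 1/(2b + 1). Correct guesses come from exact enumeration.

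| Fixed block size | Certain | Guessed correctly |
|---|---|---|
| 3 (planned) | 1/3 = 33.3% | 11/18 = 61.1% |
| 6 | 1/5 = 20.0% | 101/180 = 56.1% |
| 9 | 1/7 = 14.3% | 4021/7560 = 53.2% |

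**Randomly mixed sizes.** Simulated with 20 participants per stratum. This observer knows which sizes are in use but not the size of the current block, and uses that knowledge optimally. An observer who does not know the sizes at all would do no better.

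| Sizes | Certain | Guessed correctly |
|---|---|---|
| 3 only (planned) | 30% | 59% |
| 3 and 6 | about 7% | about 56% |
| 6 and 9 | about 5% | about 52% |

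**Price in balance.** The largest difference between arms inside an unfinished block is 1 for size 3, 2 for size 6 and 3 for size 9. The mean final difference between the largest and smallest arm was simulated with 78 participants spread at random over equally likely strata:

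| Sizes | 4 strata | 6 strata |
|---|---|---|
| 3 only (planned) | 1.5 | 1.9 |
| 3 and 6 | 1.9 | 2.4 |
| 6 and 9 | 2.3 | 2.9 |

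**The case against.** The strongest reply is that prediction needs a particular person: one who enrols or influences enrolment, knows the block size, and has seen all earlier allocations in that stratum in order. The article does not identify such a person. Recruitment runs through the hospital, neurologists, patient associations, fliers and local media, while the arms are seen by the therapists. A reader might infer that concealment has failed; the text supports only that it can be defeated. This part of the reply stands.

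Other limits also stand:
- A reader might call the trial open. That is right for participants and therapists, but the assessor is blinded.
- A reader might take 26 of 78 as the count. It is an upper bound, reached only if every stratum ends on a complete block.
- A reader might infer that one slip to the assessor reveals the rest of the block. It only leaves the other two members at 50:50, and only for an assessor who knows who shares the block. Nothing suggests that the assessor knows this.
- Several eligibility criteria are objective (age, disease stage, the cognitive score), and Table 1 puts screening and consent before allocation. That narrows the room for steering to timing and the exclusions that need judgement.
- Small blocks protect balance in a small stratified trial, so the choice of 3 has a reason.

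None of this removes the point. Concealment should not depend on staff failing to keep track, and the loss of balance from varied blocks is small.

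**Conclusion.** The point holds as an avoidable weakness of the allocation scheme. With one published block size equal to the number of arms, the last allocation of each complete block follows from the first two. That makes 22 to 26 of 78 allocations certain, depending on the number of strata (assumed to be at most 6) and how they fill, and a best guess right up to 61% of the time. These figures assume an observer who knows the block size and follows every allocation in a stratum. The arithmetic is secure. Whether anyone who enrols is in that position is not stated, so neither actual subversion nor any amount of bias in the treatment comparison is shown. The sample size and the analysis are not affected. The change is worth making because the risk is real, the list can be altered cheaply, and selection bias cannot reliably be repaired afterwards.

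**What to change.** Generate the list, or its unused remainder if recruitment has begun, with block sizes that vary at random within strata and are multiples of 3, for example 3 and 6, or 6 and 9. Do not disclose the new sizes to recruiting staff, therapists or assessors until the trial ends. The published size of 3 cannot be withdrawn, so withholding helps only for newly generated allocations. Until the end of the trial, the text of Section 2.5 could say only that permuted blocks of varying, undisclosed size are used.

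The gain is mainly in certainty: certain allocations fall from about 30% to about 5–7%, while overall guessability falls less, from about 59% to about 52–56%.

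The cost is a new list and resealing of the unused envelopes, with no change to sample size or analysis. Arm imbalance grows slightly: up to 2 (sizes 3 and 6) or 3 (sizes 6 and 9) between arms within a stratum. It can remain at the end if the last block is incomplete. Overall, the mean difference between the largest and smallest arm is about 2 to 3 participants, against 1.5 to 2 as planned. Sizes 3 and 6 suit a team that puts balance first; sizes 6 and 9 predict least.
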